### **Assessment of depression and anxiety with the HAD (Hospital Anxiety and Depression) scale.**

The patients’ psychological condition will be assessed using a self-assessment questionnaire made up of 14 items (Lepine et al., 1985). This self-assessment questionnaire is used to assess the anxiety and depression aspects felt during the last few weeks and is sufficiently sensitive to monitor the evolution of these disorders during an intervention (medication or other).

### Social adjustment assessment

The SAS-SR (Social Adjustment Scale Self-Report) scale is a simple assessment method using a self-assessment questionnaire applied to the patient’s social adjustment, notably during depressive episodes. Compared with scales based on a patient interview, the SAS-SR scale is more sensitive to changes in the clinical condition. The SAS-RS scale can contribute to the diagnosis of depressive conditions, even slight, and clinical follow-up after treatment; it can be included in the assessment criteria for longitudinal studies (Achard et al., 1995).

### Costs

Cost figures will be gathered prospectively using a healthcare consumption notebook given to the patient who will fill it in. It will be checked by the investigator at each visit (cf. healthcare consumption notebook, attached).

The point of view issued by the CPAM (Caisse Primaire d'Assurance Maladie – France’s Primary Health Insurance Fund) will be adopted to measure the direct costs corresponding to the value of the resources consumed in relation to care for the disease. We will make a distinction between:

**-** *direct medical costs* covering various aspects such as medication consumption and the use of medical resources (hospitalizations, doctor visits and consultations, lab tests and explorations),

**-** *directs non-medical costs* related to the patient’s transportation in the context of medical care.

Costs will be expressed in euros. The individual situation of patients covered by State health insurance concerning the rules for deterrent fee exemptions will be taken into account. The cost of short-term hospital stays will be measured using the applicable rates of the Groupe Homogène de Séjour (Homogenous Hospital Stay Group) following the PMSI (Programme de Médicalisation des Systèmes d’Information - Medicalized Information System Program) rules. The cost of a medium or long-term hospital stay will be measured using the daily prices applied to the number of days of hospitalization. Private practice care (medication, doctor’s visits and consultations, lab tests and explorations) will be valued on the basis of the amounts reimbursed by the French Social Security system. Transportation will be valued on the basis of the amounts reimbursed by the French Social Security system.

In conclusion, to understand the impact of the therapeutic education program in Parkinson’s disease from a medico-economic point of view, healthcare expenses will be compared for the two groups of patients during the year of the therapeutic education program.

For this, the patients’ social security numbers will be gathered. The patients’ social security numbers will be used to gain direct access to the expenses connected to their private practice care (medical consultations, physiotherapists, speech therapy, etc.) recorded at the CPAM (Caisse Primaire d’Assurance Maladie – France’s Primary Health Insurance Fund) during the protocol period and expenses connected to hospitalizations.

Data on hospitalizations will be gathered thanks to collaboration with [name], head of the DIM (Département d’Information Médicale – Medical Information Department) at the Hôtel Dieu in Toulouse. Moreover, [name] of the CPAM will help us to retrieve data relative to private practice care for patients covered by the Régime Général des Travailleurs Salariés (General Scheme for Salaried Employees).

All of this information will be gathered anonymously and the social security numbers will not be used for any other purpose.

This program’s medico-economic approach is crucial to obtaining the economic arguments needed for its continuation.

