**CONDUCT AND DURATION OF THE PROJECT**:

Within each group, the various parameters will be gathered at the baseline and then at 6 and 12 months during a normal neurology follow-up consultation. The TEP program will include an initial consultation, then individual follow-up consultations (1 to 3 per three-month period), thematic group sessions (2 or 3 per six-month period), and then an assessment consultation at the end of the 12-month period. The inclusion period will last 24 months and the total duration of the study will be 36 months.

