**4-Group sessions, Theme Days:**

Group sessions will be offered to patients who follow an education program. They will give rise to specific work depending on the theme of the day, which will be selected in relation to the participants’ educational goals.

These sessions will be held approximately every two months, during an outpatient visit, from 9:00 am to 4:30 pm. They will include 6 to 8 patients on average, as well as family members or friends who would like to attend. They are hosted by the registered nurse who accompanies the group for the whole day and a physician from the education team.

They will be structured as follows:

**Presentation session** (duration: 30 min.): Welcome, presentation of the program (duration, subjects, times, breaks, meals, location of the rest rooms) and the coordinators. Introduction round: a quick initial contact between the patients and the coordinators who are present.

**Educational sessions** lasting 40 to 45 min., separated by breaks lasting at least 10 min. to give the patients an opportunity to move around and to take their medications. There will be approximately three breaks during the day.

At the start of the afternoon, a simulation with a concrete case study will be proposed in a **wrap-up and assessment session**. This is an opportunity to take stock of how well the key points covered during the day have been understood and to prepare the transfer of the knowledge acquired into everyday life. A satisfaction questionnaire will be distributed during the last break before the Clarification Workshop session that closes out the day.

**The Clarification Workshop** is an opportunity to express one’s feelings about the day and to ask questions that the participants had not dared to ask earlier.

An individual consultation will be organized approximately once a month after the training to assess the acquisition of the knowledge and skills taught, check that they are applied and, if necessary, review those notions that were not fully understood.

**4-The Individual Assessment Consultation** is designed to highlight and promote the transformations obtained in terms of skills and improvement in quality of life.

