### Follow-up and end-of-study visits

Patients will be assessed during a normal neurology follow-up consultation at 6 and 12 months after their inclusion.

During these 2 visits, the patient:

- will receive a neurological examination with a motor rating;
- fill in the self-assessment questionnaires;
- return the completed notebook and receive the notebook for the next visit (for the visit at 6 months).
  1. Data analysis

Data will be saved using the SAS software. The data input form will correspond exactly to the paper form used for gathering data.

The data will be made anonymous before its collation.

The statistical analysis will be descriptive as well as inferential:

- Qualitative variables will be described by presenting the frequency of each modality of these variables. Quantitative variables will be analyzed to establish the median, mean, standard deviation and extreme values.

- Quality of life will be analyzed classically using a linear model including a fixed treatment effect.

Comparisons of the medical costs, motor and psychological symptomatology (secondary quantitative assessment criteria) between two treatments will also be carried out in accordance with the process described above.

1. Expected consequences of the results of the project

If the impact of a TEP program is positive in terms of quality of life and if it does not produce additional costs, this type of care will be generalized for Parkinson’s disease and will give rise to contributions at national and international conferences.

1. Provisional schedule

Start of inclusions September 2008

End of inclusions September 2010

End of patient follow-up September 2011

Analysis of the results December 2011

1. Regulatory and ethical aspects

In accordance with law No. 2004-806 of 9 August 2004 relative to public health policy and its implementing orders, the project comes within the framework of an assessment of intermediate care and the study is subject to the opinion of a CPP (Comité de Protection des Personnes Sud-ouest et Outre-Mer – Institutional Review Board of the Southwest and Overseas Possessions). The research will not be implemented until a favorable opinion is received from the CPP.

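### The costing rules do not cover the nurse-led education sessions, so the planned cost comparison cannot by itself show that the program adds no costs

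*Protocol*

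**What the plan says.** The Costs section of the Protocol sets the perspective ("The point of view issued by the CPAM"), then the items, the data sources and the prices.

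- **Items.** Direct medical costs are described as "covering various aspects such as medication consumption and the use of medical resources (hospitalizations, doctor visits and consultations, lab tests and explorations". Direct non-medical costs are those "related to the patient’s transportation in the context of medical care".
- **Sources.** A notebook kept by the patient, insurer records of private-practice care, and hospitalization data. The Experimental plan describes the notebook entries as medical consultations and hospitalizations.
- **Prices.** Short hospital stays take the stay-group tariff and longer stays a daily price. For ambulatory care, "Private practice care (medication, doctor’s visits and consultations, lab tests and explorations) will be valued on the basis of the amounts reimbursed" by social security. Transport is also valued at reimbursed amounts.

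The program is described elsewhere. The Abstract gives its intensity: "individual follow-up consultations (1 to 3 per three-month period), thematic group sessions (2 or 3 per six-month period". On theme days, the group-session section says: "They are hosted by the registered nurse who accompanies the group for the whole day and a physician from the education team".

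Two statements show what the cost result is for. The Costs section calls the economic approach "crucial to obtaining the economic arguments needed for its continuation". Under Expected consequences of the results of the project, provided that quality of life benefits and "if it does not produce additional costs, this type of care will be generalized".

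**The concern.** The education program is the one resource that differs between the groups by design. It is delivered by a hospital nurse, with a physician on theme days. A nurse-led education session at the hospital is not a hospital stay, a medication, a laboratory test or a private-practice act. It therefore fits none of the pricing rules, even if a patient happens to note it in the notebook.

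Any delivery cost missed in this way is positive in group I and zero in group II. A larger sample would not remove the error. The comparison could show a saving in other care while the staff time that produced it goes uncounted. Cost is a secondary objective, but it is one of the two conditions that the protocol attaches to generalizing the program.

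**Working it through.** The protocol states no program cost, cost standard deviation or cost margin, so there is no figure of its own to reproduce. The check has two parts.

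**1. Program components against the costing rules**

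| Component | Item listed? | Source or price given? |
|---|---|---|
| Initial consultation (nurse) | No | No |
| Individual consultations (nurse) | No | No |
| Telephone sessions | No | No; stated only to be free to the patient |
| Assessment consultations | No | No |
| Theme days (nurse and physician) | Not by name | Only if billed as hospital activity; they are held during an outpatient visit |
| Transport to sessions | Not excluded from transport | Yes, at reimbursed amounts |

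**2. Staff time per group I patient-year**

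Inputs from the Protocol:
- Initial consultation: 45 minutes = 0.75 h (Step 1).
- Individual consultations: 1 to 3 per quarter, so 4 to 12 a year (Abstract), each of 30 to 45 minutes (Step 2).
- Theme days: 2 or 3 per half-year, so 4 to 6 a year (Abstract), from 9:00 to 16:30 = 7.5 h, shared by 6 to 8 patients (Group sessions).

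Nurse time outside theme days = initial + number of individual sessions × length:
- low: 0.75 + 4 × 0.5 = 2.75 h
- high: 0.75 + 12 × 0.75 = 9.75 h

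Theme-day share per patient = days × 7.5 / attendees:
- low: 4 × 7.5 / 8 = 3.75 h
- high: 6 × 7.5 / 6 = 7.5 h

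Nurse time including theme days:
- low: 2.75 + 3.75 = 6.5 h
- high: 9.75 + 7.5 = 17.25 h

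Physician time is at most the theme-day share, 3.75 to 7.5 h. This is an upper limit because the whole-day statement attaches to the nurse and the physician's hours are not given.

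**Euros, at assumed rates not found in the protocol** (nurse 25–40 euros/h, physician 50–100 euros/h):
- Theme days captured: 2.75 × 25 = 68.75 to 9.75 × 40 = 390, so about 70–390 euros.
- Theme days not captured, no physician time counted: 6.5 × 25 = 162.5 to 17.25 × 40 = 690 euros.
- Theme days not captured, physician present all day: 162.5 + 3.75 × 50 = 350 to 690 + 7.5 × 100 = 1,440 euros.

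For 60 group I patients, the first case is 60 × 2.75 = 165 to 60 × 9.75 = 585 nurse hours.

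Telephone sessions are extra, and the protocol gives neither their number nor their length. Assessment consultations are also extra: one at about 6 months and one at the end, length not stated. At an assumed 0.5 to 0.75 h each, two would add 1 to 1.5 h.

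**The case against.** Four points on the other side deserve weight.

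- **The list is open.** The words such as mean that silence is not exclusion. The scientific justification also says that the cost of this kind of care needs to be assessed, which suggests the sponsor regards it as in scope. A reader might infer that the protocol deliberately excludes program cost, and the text does not support that. What stands is narrower: the same section goes on to fix sources and prices, and none of them reaches the nurse-led sessions.
- **The perspective is the insurer's.** Hospital staff time that is never billed is not an expense to the CPAM during the trial. A reader might infer that the comparison is wrong even on its own stated viewpoint, but that does not follow. The payer figure may be right for the payer in that year. It cannot carry a general conclusion about additional costs, because a generalized program has to be funded by someone.
- **There is no test.** A reader might take the generalization sentence as a formal decision rule. It stands under expected consequences, with no margin and no equivalence hypothesis.
- **The analysis plan is not shown.** Unit costs can reasonably be left to it. Session counts and durations cannot, because they have to be recorded while the program runs.

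**Conclusion.** The point holds. Followed as written, the costing rules understate the group I minus group II cost difference once delivery is regarded as a cost of the program, and the error favours the program.

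The uncounted part is 2.75–9.75 nurse hours per group I patient-year if theme days are picked up as hospital activity. It reaches 6.5–17.25 nurse hours plus at most 3.75–7.5 physician hours if they are not. The hours follow from the protocol's own figures. The euro amounts, about 70–390 and 350–1,440, rest on assumed hourly rates, and the upper range also assumes that the physician attends all day.

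It would be tempting to quote the upper range as the amount omitted, or to say that the omission would reverse the cost conclusion. The documents support neither: the billing of theme days is not stated, and no annual cost or cost variability is given against which to judge the amount. The direction is firm and the size is not. The problem concerns a secondary objective and the conclusion drawn from it. The primary quality-of-life comparison is untouched.

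**What to change.** 1. Log, for each group I patient, the number and length of individual, telephone, assessment and group sessions, with theme-day attendance and the physician's hours. The protocol mentions education-file records only for the initial consultation and the telephone sessions, so it should require this log explicitly.
2. Price the sessions at staff cost, dividing each theme day by its attendees, and add the result to group I direct medical costs.
3. Prevent double counting by leaving out theme days already billed as stays and transport already reimbursed.
4. Report the group I minus group II difference twice: from the CPAM viewpoint as planned, and with program delivery cost included. State that the generalization conclusion rests on the second.

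The cost is a small logging task and a set of staff unit costs. The cost result will be less favourable to the program than the payer-only figure.

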### Other clinical parameters

We will also gather the following data:

- characteristics of the patients (date of birth, sex, educational level, current job situation, living situation, current job or last job held);

- Parkinson’s disease case history (dates of the first symptoms and diagnosis);

- related comorbidities (start date and severity);

- consumption of medication (type of current treatment, daily dose, start date).

- 1. Study population

### Inclusion criteria

Only patients who met the following inclusion criteria will be accepted:

- Patients of both sexes with idiopathic Parkinson’s disease meeting the criteria in the definition of the UKPDS Brain Bank (United Kingdom Parkinson’s Disease Society Brain Bank Clinical Diagnosis Criteria, Gibb and Lees, 1988), i.e. presenting bradykinesia with at least one of the following symptoms: muscle stiffness, rest tremor at 4-6 Hz or postural instability;

- Patient with no cognitive disorders that could compromise the quality of understanding and participation by the patient in the protocol and the assessment criteria (notebooks included);

- Patient capable of filling in a self-assessment questionnaire;

- Patient benefiting from an antiparkinsonian treatment, including deep brain stimulation (for more than 3 months);

- Patient at a Hoehn and Yahr stage of ≤ 4;

- Patient having given free, informed consent and signed the consent form;

- Patient affiliated with a social security health insurance scheme.

### Exclusion criteria

The patient will not be included for the following reasons:

- Patient with an atypical non-idiopathic Parkinsonian syndrome (such as Progressive Supranuclear Palsy (PSP), Multiple System Atrophy (MSA), Corticobasal Degeneration (CBD), etc.);
- Patients with a Parkinsonian syndrome induced by a drug;
- Patient already included in a clinical trial at the time of the study;
- Patient at a Hoehn and Yahr stage of 5;
- Patient with a severe or progressive psychiatric illness or dopaminergic psychosis currently considered as being progressive;
- Patient having undergone deep brain stimulation within the last 3 months or planning to have one during the year;
- Patient incapable of understanding the protocol, filling in a notebook or any other assessment criterion or of following the clinical trial procedures;
- Patient with cognitive decline that could interfere with the assessment;
- Patient under temporary guardianship/full guardianship/judicial protection.
  1. Number of subjects required

If we want a power of 80% for a difference of 4 points in quality of life (PDQ-39), given a standard deviation of 17 points and a level of 5% in a one-tailed test, we must recruit 111 Parkinson’s patients given a correlation coefficient of 50% between the answers for the two periods. Given the potential withdrawals from the trials, we will recruit 120 patients.

The number of subjects was calculated using data from a study using the PDQ-39 quality of life scale on Parkinson’s patients (Brefel-Courbon et al., 2003).

- 1. Recruitment methods

Patients with Parkinson’s disease will be selected at the Neurology consultation services at the 2 hospitals in Toulouse (Purpan and Rangueil) by neurologists specialized in caring for Parkinson’s patients ([name], [name], [name], [name]) or at the movement disorder unit of the Neurology service at Purpan Hospital. This study seeks to be pragmatic, so we will propose this study consecutively and not selectively to all Parkinson’s patients meeting the inclusion and exclusion criteria.

We expect an average recruitment of 5 to 10 patients a month. The duration of inclusion should be 24 months.

- 1. Randomization

Randomization will be performed after the inclusion visit. It will assign the patients to one of the two groups: group I: patients following therapeutic education sessions and group II: patient receiving simple conventional medical monitoring. It will be done after verification of the inclusion criteria. It should lead to the inclusion of the number of patients needed in the study groups. This randomization will be carried out by the Centre d’Investigation Clinique (Clinical Investigation Center) at Purpan Hospital.

- 1. Conduct of the study

Each patient in the study will participate for 12 months. The total duration of the inclusion period is planned to last 2 years.

- 1. Inclusion visit

This will be done at a normal neurology follow-up consultation and will include:

- obtaining free, informed consent from the patient;

- verification of the inclusion and exclusion criteria;

- the patient’s motor score (UPDRS in the On condition for Parkinson’s patients);

- general and neurological medical examinations;

- completing the self-assessment questionnaires;

- distribution of the notebook and explanations as to how to fill it in;

- gathering the patient’s characteristics, disease data (case history, related comorbidities) and medication consumption.

All travel between the home and the hospital for pre-inclusion, inclusion and follow-up visits will be covered by the CPAM as these visits will be part of the follow-up visits for their chronic neurological disease.

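### The stated 80% power rests on an unexplained one-tailed 5% level and a single-group before-after formula; for the planned two-group comparison of 60 v 60 it is about 25% to 44%

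*Protocol*

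**What the plan says.** In the Protocol, *Number of subjects required* sets out 80% power for a 4-point difference on the PDQ-39, "given a standard deviation of 17 points", with "a level of 5% in a one-tailed test" and "given a correlation coefficient of 50% between the answers for the two periods". It concludes that "we must recruit 111 Parkinson’s patients", and adds: "Given the potential withdrawals from the trials, we will recruit 120 patients". The abstract splits the 120 into 60 per group. No reason is given for a one-tailed test or for 5% in that one tail.

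*Data analysis* says: "Quality of life will be analyzed classically using a linear model including a fixed treatment effect". It names neither a significance level nor a direction. Medical costs and the other quantitative secondary criteria are to be handled in the same way.

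The main objective is directional and between groups: better quality of life with the education programme than without it. The study is open, and the main criterion is a questionnaire that patients complete themselves. Under *Expected consequences of the results of the project*, wider adoption depends on a positive quality-of-life result together with a cost condition: "if it does not produce additional costs, this type of care will be generalized".

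**The concern.** Two choices in the sample size section make the stated power look better than it is.

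The first is the level. A one-tailed 5% test uses the same critical value as a two-sided 10% test. In an open trial with a self-reported outcome, knowing one's allocation can by itself shift answers towards the education group. That is the direction in which the evidence threshold has been relaxed.

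The second is the formula. A correlation between two periods enters a before-after calculation in one group of patients, whereas the objective and the linear model compare two independent groups. If the number comes from the first setting and the analysis from the second, the 80% describes a test that will not be performed.

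What is at stake is how the result is read. A null result from a trial believed to have 80% power would be taken as fair evidence against a 4-point benefit. At 25% to 44% power it would say little. A positive result is meant to support wider adoption, so the standard it meets should be explicit and conventional.

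**Working it through.** **Inputs, all from the Protocol.** Difference d = 4; SD = 17; correlation r = 0.5; power 80% (z = 0.842); one-tailed 5% (z = 1.645); 111 patients, 120 recruited, 60 per group. For comparison, two-sided 5% has z = 1.960. Normal approximations are used throughout.

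**1. Reproducing the Protocol's figure.** The SD of a within-patient change is 17 × √(2 × (1 − 0.5)) = 17. For one group measured twice:

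n = (1.645 + 0.842)² × 17² × 2(1 − 0.5) / 4² = 111.67

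This matches 111 (112 if rounded up). With 1.960 in place of 1.645, n = 141.8, so the figure does use the one-tailed level.

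**2. Effect of sidedness alone, on that same formula.** With 120 patients, d/SE = 4 × √120 / 17 = 2.578.

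- One-tailed: Φ(2.578 − 1.645) = 82%.
- Two-sided: Φ(2.578 − 1.960) = 73%.

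With 111 patients the two values are 80% and 70%.

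**3. The comparison actually planned, 60 v 60.**

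- Change score: SE = 17 × √(2/60) = 3.10, so d/SE = 1.289. Power is Φ(1.289 − 1.645) = 36% one-tailed and Φ(1.289 − 1.960) = 25% two-sided.
- Baseline-adjusted: residual SD = 17 × √(1 − 0.5²) = 14.72, SE = 14.72 × √(2/60) = 2.69, so d/SE = 1.488. Power is 44% one-tailed and 32% two-sided.
- With only 111 patients analysed (55.5 per group on average), power is 34% and 24% on change scores, and 42% and 30% baseline-adjusted.

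**4. Size needed for 80% power with two groups.** Per group, n = 2 × (z sum)² × SD² / 4².

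| Analysis | One-tailed 5% | Two-sided 5% |
|---|---|---|
| Change score (SD 17) | 224 per group, 448 in all | 284 per group, 568 in all |
| Baseline-adjusted (SD 14.72) | 168 per group, 336 in all | 213 per group, 426 in all |

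Put the other way, 60 per group on change scores gives 80% power for a difference of (1.645 + 0.842) × 3.10 = 7.7 points one-tailed, or (1.960 + 0.842) × 3.10 = 8.7 points two-sided.

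**5. A more favourable model.** Suppose the analysis uses the mean of the 6- and 12-month scores adjusted for baseline, with correlation 0.5 between every pair of visits. The residual variance is 17² × (0.75 − 0.25) = 144.5. Power at 60 per group is then 57% one-tailed and 45% two-sided. The one-tailed requirement is 112 per group, 224 in all.

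**6. How much is due to each choice.** For two groups, moving from one-tailed to two-sided costs 11 to 12 percentage points. Most of the gap from 80% comes from the formula.

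**The case against.** The best defence is that a one-tailed test fits the directional objective, that the Protocol declares it openly, and that it holds its stated 5%. All of that is true. It does not supply a reason for placing the full 5% in one tail, and it does not affect the formula.

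It can also be said that 111 was meant per group, since step 5 gives 112 per group for one two-group model. The Protocol, however, treats 111 as the whole trial and rounds it up to 120. On that reading, 120 patients give 57%, still well short of 80%.

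Three stronger readings are tempting, and the Protocol does not support them.

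- *That the data analysis section contradicts the one-tailed sizing.* It is silent on direction, and a treatment effect in a linear model can be tested either way. Direction may also be settled in a statistical analysis plan that is not shown.
- *That the roll-out statement doubles the false-positive risk.* The 5% is double only in comparison with the 2.5% favourable tail of a two-sided 5% test, which the Protocol does not adopt. Requiring a cost condition as well can only lower the chance of a wrong roll-out. In simulation with no true effect on either outcome and correlations from −0.3 to 0.3, that chance was 1.3% to 3.7% if the observed cost difference had to be zero or less. It was 4.3% to 5.0% if costs merely had not to be significantly higher. No one-tailed cost test is specified.
- *That the pilot experience signals harm because prognosis was discussed.* The scientific justification reports better acceptance of the disease, better compliance and easier relations with caregivers and physicians.

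**Conclusion.** The point stands in two parts. The one-tailed 5% level is unexplained and lenient for an open trial with a self-reported main criterion: the chance of wrongly declaring benefit is 5%, against 2.5% under a two-sided 5% test. And the 80% is not the power of the planned between-group analysis, which is about 36% or 44% at one-tailed 5% and about 25% or 32% at two-sided 5%. The formula is the larger fault and sidedness the smaller.

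These figures take the Protocol's SD, difference and correlation as given. They assume that 17 is the SD of scores at a single visit, that 0.5 is the correlation between baseline and follow-up, and that allocation is equal. The sizing formula is inferred, because the Protocol does not print it, but it reproduces the stated total. Averaging both follow-up visits raises power to 57% or 45% and does not change the conclusion.

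**What to change.** In both *Number of subjects required* and *Data analysis*, state one and the same test for the PDQ-39: two-sided at 5%, with a 95% confidence interval for the between-group difference. The directional hypothesis can stay in the objectives.

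Replace the 80% by the power of the two-group comparison with 120 patients, for the model that will be used: about 25% on change scores or 32% baseline-adjusted at two-sided 5%. The 73% from step 2 should not be used, as it keeps the single-group formula.

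Report the cost difference with a two-sided 95% confidence interval. Wider adoption depends on the absence of additional costs, and a non-significant difference would not by itself show that.

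The cost is wording in a few places and a much less favourable stated power. No extra patients or data are needed to make the statement correct. Reaching 80% two-sided would take 426 to 568 patients on the models in step 4, which is a separate decision for the sponsor.
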